**Methods:**

In this population-based retrospective cohort study, we will use clinical and health administrative data of older adults (65+ years of age) who received publicly funded continuing care in the community in the Canadian provinces of Alberta, British Columbia, and Manitoba between January 1, 2012, and December 31, 2024. We will compare patterns of day program use between provinces and assess changes over time. We will then compare characteristics of older adults (eg, age, sex, physical or cognitive disability, area-based deprivation indices, and caregiver availability or distress) by pattern of day program use or nonuse, province, and time. Finally, we will create a propensity score–matched comparison group of older adults in the community, who have not attended a day program. Using time-to-event models and general estimating equations, we will assess whether day program attendees compared with nonattendees enter care homes later; use emergency, acute, or primary care less frequently; experience less cognitive and physical decline; and have better mental health.

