## Methods

### Study Design

Using an integrated knowledge translation (iKT) approach [51,52], we partnered with a cross-Canadian team of experts to design this population-based retrospective cohort study (ClinicalTrials.gov; NCT06440447) covering the Canadian provinces of Alberta, British Columbia, and Manitoba, and we will collaborate with our experts throughout the study. Experts include older adults (some with dementia), their caregivers, Alzheimer societies, caregiver organizations, day program staff and managers, and government and health system decision makers. They will provide intimate knowledge of day programs, and the experience of attending them or caring for an attendee, which will help us interpret and contextualize our findings. We will use deidentified clinical and health administrative data from each of the 3 provinces. Our study will follow the STROBE (Strengthening the Reporting of Observational Studies in Epidemiology) [53], and the REporting of studies Conducted using Observational Routinely-collected health Data (RECORD) [54] guidelines. Provincial data policies require data to remain in each respective province, preventing linkage across provinces and analyses of all data in one place. Therefore, in-house data analysts with each provincial health system will carry out the analyses separately with shared protocols and programs.

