### Setting and Sample

Our study settings are community-based continuing care systems. Each province provides access to a range of publicly funded community-based continuing care services, including adult day programs [55-63]. Each provincial health system determines and enacts access criteria and provides services (directly or via contracted providers) [55-63]. Day program eligibility is assessed in each province, using comparable processes, criteria, and assessments (ie, the Resident Assessment Instrument—Home Care [RAI-HC], a standardized, valid, reliable assessment tool [64]) [60,65,66]. To be eligible, attendees need to have not only some care dependency but also the ability to cope to some extent with activities of daily living, ambulate or transfer with no or minimal assistance, be continent or independent in managing continence products, exhibit no or easily manageable responsive behaviors, and either be alone for extended periods or have a caregiver who requires respite. Our study cohort will include all individuals aged 65 years or older with an initial RAI-HC assessment completed between January 1, 2012, and December 31, 2021. We will follow everyone until they move into a care home, are lost to follow-up (eg, because of death, moving out of province, loss of public insurance eligibility), or until December 31, 2024 (the end of the period covered by our data). That will allow for a care trajectory of at least 3 years (for those with an initial RAI-HC assessment in December 2021), enabling us to assess the number and characteristics of individuals with different day program use patterns, and compare them with those who were never exposed to a day program.

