### Sample Size Calculation

The yearly average number of completed RAI-HC assessments is ~20,000-30,000 in Alberta, ~34,000-39,000 in British Columbia, and ~10,000 in Manitoba [67]. About 50% of those assessed receive a reassessment within 12 months and another 10%-30% receive a reassessment after >15 months [68]. There are 89 publicly subsidized day programs in Alberta (~3300 spaces per day), 95 in British Columbia (~1500 spaces per day), and 70 in Manitoba (~1000 spaces per day) for a total of 254-day programs with 5800 spaces on any given day. Some day program users do not attend daily, but only 1 or a few days per week, so the number of unique attendees exceeds the number of spaces per day. This corresponds to >20,000 attendees per year (>200,000 within the study period), each with multiple assessments. Our study sample size will be large enough to detect small effects sizes. With Cox proportional hazards models, adjusted for covariates explaining an assumed 25% of effect variance (a=.05; power=0.8) [69], we require a total sample of 1327 participants to detect a hazard ratio for admissions to care homes of 0.6 (as can be expected based on a similar Canadian study [42]) in favor of day program attendees. Similarly, Kelly [43] was able to detect significantly fewer emergency department visits and hospital admissions per day among 812 day program attendees compared with 812 propensity score matched to nonattendees. Our expected sample size will be considerably larger than for those previous studies, allowing for complex statistical modeling.

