#### Objective 3: Assess Effects of Day Programs

To create a propensity score, we will run a logistic regression for each province with day program attendance or nonattendance as the dependent variable and adding matching covariates. We will use one-to-one matching (1 matched nonattendee for every attendee) [78]. We will use matching without replacement [85] and apply an optimal caliper matching algorithm [86]. As per best practice recommendations [87], we will use a caliper width of 0.2 of the SD of the propensity score’s logit. If this matching approach does not allow us to achieve a sufficient sample size, we will use propensity score quintiles for matching.

We will compare sample characteristics and study outcomes between attendees and nonattendees in every year and province, using bivariate statistical tests (eg, chi-square test or Fisher exact test for categorical variables, *t* tests, or ANOVAs for continuous variables, and their nonparametric equivalents if variables violate statistical assumptions). To assess the effect of day program exposure on time to care home admission, we will specify a multilevel time-to-event model with a health region–level random effect [88]. Health systems in each of the 3 provinces are divided into 5 health regions [89-91], and regional policies may cause clustering effects that our models must account for. Each model will include day program use or nonuse class as independent variable and will be adjusted for time-varying variables. These will include matching variables, if appropriate (ie, in case of group differences in matching variables over time or due to missing data) [80-82] and, if needed, additional covariates (eg, demographics, social determinants, medical or functional conditions, and non–day program community care). Covariates that differ between attendees and nonattendees with a *P* value of ≤.15 in the bivariate analyses will be considered for inclusion. We will add covariates stepwise, one-by-one, and remove those that cause collinearity issues or decrease model fit. As in objective 2, we will pool provincial effects statistically, using random-effects mixed regression models.

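### The P ≤ .15 stepwise screen picks adjustment covariates by cell size and number of looks rather than by imbalance, so the pooled provincial effects may not be adjusted alike

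*Protocol article*

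**What the plan says.** All of this comes from the protocol article; no separate analysis plan is at hand.

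- *Objective 3: Assess Effects of Day Programs* sets the tests: "We will compare sample characteristics and study outcomes between attendees and nonattendees in every year and province, using bivariate statistical tests". These are the only bivariate analyses that the section describes.
- The same section sets the screen: "Covariates that differ between attendees and nonattendees with a *P* value of ≤.15 in the bivariate analyses will be considered for inclusion". The next step is: "We will add covariates stepwise, one-by-one, and remove those that cause collinearity issues or decrease model fit".
- Models are fitted separately in each province and the provincial effects are pooled with random-effects models. The section's closing paragraph carries the same stepwise approach to the GEE models for all other outcomes.
- *Study Design* gives three provinces ("covering the Canadian provinces of Alberta, British Columbia, and Manitoba"). The number of years is 13 if it means years of data ("between January 1, 2012, and December 31, 2024" in the abstract) or 10 if it means years of cohort entry ("initial RAI-HC assessment completed between January 1, 2012, and December 31, 2021" in *Setting and Sample*).
- *Objective 2*, by contrast, reports quarterly and provincial distributions of characteristics descriptively, as proportions with 95% CIs, before any modelling.

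**The concern.** A covariate needs adjustment because it is imbalanced and predicts the outcome. The screen measures neither directly. Its P value mixes the size of the imbalance with the number of people in the cell. Because the tests are repeated by year, it also depends on how many chances a covariate gets to pass. The plan names no cell as the deciding one and gives no rule for reducing 10 to 13 P values per province to one decision. Nor does it tie the screen to the matching index date.

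The later stepwise step does not repair this. Removal for collinearity or worse fit is not a check for confounding, and it cannot bring back a confounder that the screen left out.

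What is at stake is comparability. *Study Design* promises shared protocols and programs, and *Objective 2* appeals to consistent regional analyses. A screen driven by provincial cell size can still give different covariate sets under identical code. Effects adjusted for different things would then be pooled as if they were one quantity, for every objective 3 outcome.

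**Working it through.** The document states no number of tests and no error rate for these comparisons, so there is no figure of its own to reproduce here. Its sample size of 1327 for the Cox model is not at issue. Cell sizes are not given either; those below are assumptions.

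**1. Dependence on cell size.** For a two-sided comparison of two groups of n with unit variance, P = .15 corresponds to |z| = 1.44. The standardized difference that just passes is 1.44 × √(2/n). For a true difference d, the test statistic is centred at d × √(n/2).

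| Assumed n per group | Difference giving P = .15 | Chance that a true 0.10 passes one test |
|---|---|---|
| 200 | 0.144 | 34% (missed 66%) |
| 1,000 | 0.064 | 79% |
| 5,000 | 0.029 | over 99.9% |
| 6,667 | 0.025 | over 99.9% |

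For n = 200 the centre is 0.10 × √100 = 1.0, and P(|Z + 1.0| < 1.44) = Φ(0.44) − Φ(−2.44) = 0.66. The last row takes the figure in *Sample Size Calculation* ("This corresponds to >20,000 attendees per year (>200,000 within the study period), each with multiple assessments") and splits 20,000 equally over three provinces.

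The provinces are not equal. The same section lists about 3300 day program spaces per day in Alberta and about 1000 in Manitoba. If attendees followed spaces, the passing difference in Manitoba would be √(3300/1000) = 1.8 times that in Alberta. The same imbalance could then pass in one province and fail in the other.

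**2. Number of looks.** Suppose any year may qualify a covariate. The models are provincial, so the relevant family is one province. For a perfectly balanced covariate and independent tests:

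- one test: 15%
- 10 years: 1 − 0.85^10 = 80%
- 13 years: 1 − 0.85^13 = 88%

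The same people recur from year to year, so independence is generous. With first-order autoregressive correlation between years (simulation, 200,000 runs, 13 years), the figure is 67% at a correlation of 0.8 and 41% at 0.95.

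**3. Outcome comparisons (secondary).** Expected chance differences = years × provinces × outcomes × level. The level of .05 is an assumption: the document gives it only for the Cox sample size. *Study Outcomes* yields 11 outcomes if each example of primary or specialist care counts once (1 care home admission + 1 depression + 2 decline + 4 care use + 3 emergency and hospital use). It yields 8 if those four count as one, and 12 if caregiver distress from objective 3 is added. With no true effects:

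- low: 10 × 3 × 8 × .05 = 12.0
- middle: 13 × 3 × 11 × .05 = 21.5
- high: 13 × 3 × 12 × .05 = 23.4

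**The case against.** The strongest defence has four parts.

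*The screen is softer than an automatic rule.* A covariate with P ≤ .15 is only a candidate, is added if needed, and can be removed. No any-year rule is written. This stands: the 80–88% is conditional on one reading. But no other reading is given, and the dependence on cell size needs no such reading.

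*Over-inclusion does little harm, and the two errors do not occur under the same rule.* If any of 13 independent years could qualify a covariate, a difference of 0.10 missed 66% of the time per cell would be missed in all of them with probability 0.66^13, about 0.5%. This stands too. False inclusion belongs to the any-year reading and false exclusion to a single-test reading in small cells; they should not be added together. At the scale the article expects, over-inclusion is the likelier fault. The plan still does not say which of the two behaviours it has.

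*Confounding control rests mainly on matching.* *Propensity Score–Matching Variables* matches on the eligibility variables whatever the screen does, adds a second set from objective 2, and *Objective 3* lets matching variables re-enter if groups differ. This limits the bias but does not make the remaining adjustment the same across provinces.

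*Balance at the index date will not show later differences*, while the models adjust for time-varying variables. True. The proposed set governs which baseline covariates enter and does not bar prespecified time-varying terms.

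A reader might also infer that about 21 false outcome findings will enter the trial's conclusions. The document does not support that. The count is not fixed, the outcome tests carry no decision rule, and their P values feed neither the covariate screen nor the adjusted, pooled models. Nor should a 39-cell family (13 years × 3 provinces) be used for the screen, since models are fitted by province. Missing multiplicity control is not pressed, as an analysis plan may cover it.

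**Conclusion.** The point holds for the covariate screen. As written, it selects by cell size and, if more than one year may count, by number of looks. A standardized difference of 0.029 passes at an assumed 5,000 per group, while at an assumed 200 per group a true 0.10 fails a single test about two times in three. Under an any-year reading a balanced covariate passes within a province 80–88% of the time if tests are independent, and about 41–67% over 13 strongly correlated years, against a nominal 15%.

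The consequence is that pooled effects may not be adjusted alike. That they will differ is not shown, no bias in any effect estimate has been quantified, and matching limits it. The outcome tests are a reporting matter: roughly 12 to 23 chance differences at an assumed .05 with no true effects, which could be misread as year- or province-specific effects but do not touch the main estimates. The change is worth making before analysis; it does not call the design into question.

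**What to change.** Replace the P ≤ .15 stepwise screen with one covariate set used in all three provinces and for every objective 3 model of a given outcome. It would contain:

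1. outcome predictors prespecified on subject-matter grounds, including any time-varying terms the models are to carry; and
2. every baseline covariate whose absolute standardized difference at the matching index date, after matching, exceeds a prespecified limit in any province. A limit of 0.1 is an example; the document gives none.

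Report the year-by-province outcome comparisons as estimates with 95% CIs, labelled descriptive and without tests, in line with the descriptive reporting in objective 2.

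The cost is a change of wording and an edit to the shared program, with no new data. Provinces need to exchange only their balance tables, not individual records. The downside is a few more covariates in each provincial model, which is negligible at the expected sample size.

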#### Propensity Score–Matching Variables

To compare outcomes between day program attendees and nonattendees, we will use propensity score matching [78] (for details, see Statistical Analyses section). Propensity scores aim to ensure a similar distribution of baseline variables among treatment (day program attendees) and control (nonattendees)—akin to what random assignment aims to accomplish in randomized trials [78]. Since we lack evidence on differences between day program attendees and nonattendees, our objective 2 analyses will be key to informing the selection of the exact covariates that will form the propensity score. We will derive covariates for day program attendees from the RAI-HC day program eligibility assessment (index date). For each day program attendee, we will identify potential matches as nonattendees whose first RAI-HC assessment was completed within ±3 months of the attendee’s index date (ie, admission to long-term home care at about the same time). This RAI-HC assessment will provide the relevant covariates to enable propensity score matching with day program attendees as of their index date.

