Using GEEs and a similar approach as for the time-to-event models (including separate models in each province and statistical pooling of their effects), we will assess whether the other study outcomes differ by day program use or nonuse pattern. Models will include each study outcome of interest as a dependent variable, day program use or nonuse class and time of assessment as independent variables, and similar covariates (using the same stepwise approach) as the time-to-event models. Models will also include a random term to account for repeated measures within individuals. The choice of a link function will be informed by the nature of the variable and theoretical and empirical considerations. For example, the number of hospital, emergency department, or physician visits has been shown to follow a zero-inflated negative binomial distribution, sometimes requiring an offset for the natural logarithm of person-time [92]. For continuous outcomes (eg, days spent in hospitals), we will use an identity link function, and for dichotomous outcomes (eg, presence or absence of depressive symptoms), we will use a logit link function. All models will apply multiple imputation in case of missing data, which we expect to be small based on our previous work with the administrative health care data sources used in this study.

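### Outcomes of 1:1 matched attendees and nonattendees are analysed without the matched pair, which makes the unadjusted comparisons conservative to the extent that the matching variables predict outcome

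*Protocol article*

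**What the plan says.** All of this is in the Protocol article, mostly under Statistical Analyses, Objective 3: Assess Effects of Day Programs.

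- Matching ratio: "We will use one-to-one matching (1 matched nonattendee for every attendee").
- Algorithm: "We will use matching without replacement [85] and apply an optimal caliper matching algorithm", and "we will use a caliper width of 0.2 of the SD of the propensity score’s logit". Each matched person therefore belongs to exactly one pair.
- Candidate controls, under Propensity Score–Matching Variables, are "nonattendees whose first RAI-HC assessment was completed within ±3 months of the attendee’s index date".
- Fallback: "If this matching approach does not allow us to achieve a sufficient sample size, we will use propensity score quintiles for matching".
- Scope of the group comparison: it covers study outcomes as well as sample characteristics, and is made separately for each year within each province.
- Tests named for that comparison: "using bivariate statistical tests (eg, chi-square test or Fisher exact test for categorical variables", with t tests or analysis of variance for continuous variables and nonparametric counterparts where assumptions fail. No paired form is named.
- Time-to-event model: a random effect for health region is the only dependence term.
- GEEs: "Models will also include a random term to account for repeated measures within individuals". Again no pair.
- Matching variables enter the models only where the groups come to differ on them over time or because of missing data.

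**The concern.** The score is built first from the eligibility items: physical function, cognition, behaviour, continence, caregiver availability and caregiver distress. Several of these are baseline levels of the study's own outcomes, and the others plausibly bear on care home admission and service use. Two people with nearly the same score may then have positively correlated outcomes.

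A test that treats the groups as independent uses a variance that is too large for the difference between matched groups. P values come out too high, intervals too wide, and a real difference is easier to miss. The article undertakes to establish whether effects are positive, negative or absent, so a bias towards finding nothing matters.

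The conditional adjustment rule adds to this. Adjusting for the matching variables would remove most of the problem, but good matching removes the group differences that trigger adjustment. The better the match, the likelier the adjustment is left out.

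**Working it through.** **Figures in the plan.** The article gives no within-pair correlation and no operating characteristics for the matched comparison, so there is nothing to reproduce on this point. Its one power figure, 1327 participants under Sample Size Calculation, depends on an event probability that is not stated. The two-sided Schoenfeld formula gives 120.3 events for a hazard ratio of 0.6, and 120.3/0.75 = 160.4 after the 25% covariate allowance. An N of 1327 then implies an event probability of 160.4/1327 = 0.121. The figure can be neither confirmed nor refuted, and this point does not rest on it.

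**Closed form.** Let rho be the within-pair outcome correlation (assumed), with equal variances in the two groups.

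- Variance of the matched difference relative to the independent-group variance: 1 − rho.
- True size of a nominal 5% unpaired test: 2 × [1 − Φ(1.96/√(1 − rho))].
- Ratio of unpaired to correct interval width: 1/√(1 − rho).
- Power of the unpaired test where the paired test has 80%: 1 − Φ(1.96/√(1 − rho) − 2.80).

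For rho = 0.2: √0.8 = 0.894 and 1.96/0.894 = 2.19. Size is 2 × [1 − Φ(2.19)] = 2.8%, width ratio is 1/0.894 = 1.12, and power is 1 − Φ(2.19 − 2.80) = 72.9%.

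| Assumed rho | True size | Width ratio | Unpaired power (paired 80%) |
|---|---|---|---|
| 0.05 | 4.4% | 1.03 | 78.5% |
| 0.1 | 3.9% | 1.05 | 76.9% |
| 0.2 | 2.8% | 1.12 | 72.9% |
| 0.3 | 1.9% | 1.20 | 67.7% |
| 0.5 | 0.6% | 1.41 | 51.2% |

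**Simulation with no true effect.** There were 1,500 runs per scenario, five covariates, nearest-neighbour 1:1 matching without replacement within 0.2 SD of the logit, and about 300 pairs. R² is the assumed share of outcome variance (for the binary outcome, of its underlying continuous scale) explained by the matching covariates.

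| Outcome, R² | Pair correlation | Unpaired | Paired | Covariate-adjusted, no pair term |
|---|---|---|---|---|
| Continuous, 0.10 | 0.08 | 4.5% | 5.1% | 5.5% |
| Continuous, 0.25 | 0.21 | 2.7% | 4.8% | 5.1% |
| Continuous, 0.50 | 0.43 | 1.1% | 5.1% | 4.9% |
| Binary, 0.25 | 0.13 | 3.5% | 4.5% | 4.5% |
| Binary, 0.50 | 0.28 | 1.9% | 5.1% | 4.6% |

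A second simulation (6,000 people, binary outcome) varied how strongly the score predicts outcome. With log-odds rising by 0.5, 1.0 and 1.5 per SD of the score, the pair correlation was 0.04, 0.14 and 0.27. Unpaired size was 5.3%, 3.0% and 1.3%; paired size was 5.9%, 5.1% and 4.2%. The Monte Carlo standard error at 5% is √(0.05 × 0.95/1500) = 0.6 percentage points, so the weakest scenario shows no real difference.

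**Limits.** Matching here was greedy rather than optimal, and the effect was a difference in means or proportions rather than a hazard ratio. In the five-covariate simulation the outcome depended on the covariates in the same combination as the score, which favours a high pair correlation. The figures show direction and order of size only.

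**The case against.** **The effect analyses are the models, not the bivariate tests.** This largely stands. The bivariate tests are preliminary comparisons and a covariate screen, and every size figure above for unpaired analysis is unadjusted. Adjusting for the matching covariates without a pair term brought size back to 4.5% to 5.5%. What remains is that the plan makes that adjustment conditional.

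**The correlation is unknown and may be small.** This stands. The score predicts attendance, not outcome. Marked distortion in the second simulation needed odds ratios of about 2.7 and 4.5 per SD (exp 1.0 and exp 1.5), and the documents do not show links that strong. The ±3-month window adds little to the bivariate tests, which are already run by year.

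**The study is large.** This stands for power in the full sample. At four times the size that gives 80% paired power, the unpaired test still has about 99.9% power at rho 0.3 (1 − Φ(2.34 − 5.60)). It does not stand for interval width: 1/√(1 − rho) does not depend on N.

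**The test list is only exemplary, and an article leaves variance estimators to a fuller document.** This does not carry the point. The article names its tests and its dependence terms, and states that clustering must be handled. It covers region and person and omits the dependence its own matching creates.

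**Simple paired tests would not fit.** This stands and shapes the fix. The exposure is a use-class variable with several levels, so contrasts between classes run across pairs. Yearly paired tests lose pairs with a missing member, and the quintile fallback has no pairs.

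**Conclusion.** The plan should be corrected, within limits. The unadjusted outcome comparisons are conservative to the extent that the matching variables predict outcome: for an assumed rho of 0.1 to 0.3, true size is 3.9% to 1.9% and intervals are 5% to 20% too wide. Below about 0.05 the effect can be ignored. Time-to-event and GEE models that leave out the matching variables share the problem, but by how much has not been worked out here.

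A reader might infer more: that false positives are inflated, or that the error rates of every day program effect estimate are wrong. The documents support neither. Positive pair correlation pushes the error the other way. No value of rho is given, and a model that does adjust for the matching variables has close to nominal size. The P ≤ .15 screen uses the same tests, but passing it only makes a covariate a candidate for inclusion.

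The conclusion assumes a positive within-pair correlation, equal variances for the closed form, and that the 1:1 match rather than the quintile fallback is used.

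**What to change.** - Carry the matched-pair identifier into the analysis file.
- For outcome comparisons, use regression with robust variance clustered on the pair. This handles use-class contrasts and pairs with a missing member. Keep McNemar or the paired t test for simple attendee-versus-nonattendee comparisons in complete pairs.
- In the GEEs, make the pair the cluster, with both members' repeated assessments inside it. Within-person correlation is still covered.
- In the time-to-event model, use pair-clustered variance. If the software cannot combine this with a region random effect, enter region as a stratum or fixed effect.
- Adjust all models for the baseline matching covariates as a rule, not conditionally.
- If the quintile fallback is used, stratify by quintile.

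Cost: revised wording and modest changes to the programs shared across provinces, with no new data. The downsides are little gain where the matching variables are weakly prognostic, and possibly a minor change to how region is modelled. If the investigators prefer to ignore the pairs, they should say so and give the reason.
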